**Figure d38e602:**
[figure not shown]

Ressing et al proposed a seven-level scale ranging from + 3 (very hypertonic) to − 3 (very hypotonic), with 0 being normal tone. Superficial layers of the PF muscles, including the ischiocavernosus, bulbocarvernosus and transverse superficial, can be assessed by intravaginal palpation at 3, 6, and 9 o’clock. The deeper layers are evaluated at 3, 6, and 9 o’clock for the pubococcygeus sling and at 5 and 7 o’clock for the iliococcygeus. This scale has been studied for its interrater reliability, and overall, a fair to moderate reliability was found, with correlation coefficients of 0.230 to 0.514.^[15]^

##### Change in HA (in cm^2^) assessed by perineal 3D USG

2.7.2.2

2A. PF examination by perineal 3D USG. Examination will be carried out using a Volunson-i BT11 USG console, volume contrast imaging software (GE Healthcare Austria GmbH, Zipf, Austria) and a RAB4-8-RS 3D/4D 4 to 8 MHz probe in the midsagittal plane. Examination will take place with an empty bladder in the lithotomy position. The probe will be placed longitudinally on the perineum. A 3D image of the HA will be taken at rest, at maximum contraction and with the VM. This method was tested for reliability and shown to be very good.^[6,7]^

2B. PF examination by perineal 2D USG. The distance between the symphysis and levator ani angle (L-H) will be measured at rest and during contraction. Examination will be carried out using a Volunson-i BT11 USG console, volume contrast imaging software (GE Healthcare Austria GmbH, Zipf, Austria) and a RAB4-8-RS 3D/4D 4 to 8 MHz probe in the axial plane using render mode. Examination will take place with an empty bladder in the lithotomy position. The probe will be placed longitudinally on the perineum to measure the L-H transversal distance inferior margin symphysis and puborectal sling of the anorectal angle at rest and during maximal contraction of the PF muscles. This method was tested for reliability and found to be very good.^[6,7]^

The USG examinations will be carried out in cooperation with a trained urogynecologist.

##### Change in I-QoL

2.7.2.3

The I-QoL is composed of 3 subscales (avoidance and limiting behavior, psychosocial impact and social embarrassment) and is comprised of 22 questions with a total score in the range from 0 (worst QoL) to 100 (best QoL). Cronbach alpha reliability of the I-QoL is 0.91 to 0.96.^[17]^

##### Change in PGI-I

2.7.2.4

The PGI-I evaluates the status of urinary problems compared to the patient's condition before treatment in the study. Patient impressions are evaluated according to the following scores:

1.much better;2.quite better;3.a little better;4.no change;5.a little worse;6.a lot worse; and7.definitely worse.^[18]^

#### Adverse events/harms

2.7.3

Any adverse event during the research period will be registered and considered for data analysis. Interventions will be interrupted, if any risks to participants are identified. It is important to mention that the risks presented in the study will be minimal, such as musculoskeletal pain resulting from exercise.

### Adherence

2.8

Eligibility, cooperation and safety will be recorded during recruitment and implementation of the study. The investigator will register eligible patients from all outpatient databases. The number of eligible patients from all patients included will be recorded. During the period of intervention, cooperation and adherence, as well as discontinuation of treatment, will be recorded. Adherence to intensity of treatment will be secured.

### Data analysis

2.9

Descriptive and analytical statistics will be used for data analysis. An unpaired *t* test will be used to compare the experimental and control groups before training. Differences between the control and experimental groups at pre- and post-intervention will be assessed using a generalized linear model repeated-measures mixed-design ANOVA (significance level, *P* < .05), and partial eta-squared (η^2^) effect sizes will be calculated. According to Cohen's (1988) specification for ANOVA analysis, effect sizes were classified as follows: η^2^ = 0.00–0.003, no effect size; η^2^ = 0.010–0.039, small effect size; η^2^ = 0.060–0.110, medium effect size; and η^2^ = 0.140–0.200: large effect size. Calculations will be evaluated in IBM SPSS 25 Windows (IBM, Chicago, IL).

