### Sample size

2.3

We used an estimate according to selection of the sample of probands based on the test strength of 0.80 and alpha = 0.05 (type I error). The number of probands in the Group A and Group B will be 34 in each, giving a total of 68. We expect a 20% loss, so we will include 86 probands. Based on sample selection, we expect a decrease in incidence after intervention from 25% to 10%. We will consider the treatment to be successful if there is a decrease of more than 50%.

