##### Change in IEF over 1 week

2.7.1.1

Urine leakage symptoms were reported according to an assessment of the number of incontinence episodes per week (or IEF).

SUI is confirmed with a positive score on the ICIQ-UI and a negative symptom score on the overactive bladder questionnaire (OAB-q). Both overactive bladder and urge urinary incontinence were excluded by the OAB-q.

The International consultation on urinary incontinence questionnaire short form (ICIQ-UI SF) was developed by the ICS. The first 2 questions on the ICIQ-UI monitor the frequency and quantity of leaked urine, and the third question considers how urine loss affects the daily lives of women. The ICIQ-UI score is the sum of all questions (0 = no leak; 1–5 = slight; 6–12 = moderate; 13–18 = severe; 19–21 = very serious). Cronbach alpha reliability is 0.95.^[10,11]^

The OAB-q focuses on the symptoms of an overactive bladder over the last 4 weeks. It contains 6 questions on symptoms, giving the symptom score (0, without symptoms; 100, most symptoms), and 13 questions that assess QOL (100, best QOL; 0, worst QOL). Cronbach alpha is 0.90.^[12,13]^

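### The planned pre/post mixed ANOVA for weekly incontinence episodes has no baseline covariate; ANCOVA on baseline would answer the same question more precisely, at no extra data cost

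*Protocol article*

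**What the plan says.** All of the following is in the protocol article.

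- **Primary outcome (2.7.1.1).** IEF comes from "an assessment of the number of incontinence episodes per week". Section 2.7 has outcomes measured before treatment and over the 12 weeks, so each woman has a baseline count.
- **Question (1.1 and 2.1).** The objective is worded as change in IEF over 12 weeks. The hypothesis is between groups: fewer episodes after high- than after low-intensity training.
- **Analysis (2.9).** "Differences between the control and experimental groups at pre- and post-intervention will be assessed using a generalized linear model repeated-measures mixed-design ANOVA", with partial eta-squared as the effect size. Despite the word generalized, ANOVA with partial eta-squared is a normal-error linear model. No covariate is listed.
- **Baseline comparison (2.9).** An unpaired t "test will be used to compare the experimental and control groups before training".
- **Size (2.3).** "The number of probands in the Group A and Group B will be 34 in each, giving a total of 68". Allocation is 1:1 (2.2).

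**The concern.** A mixed ANOVA with two groups and two time points offers two terms that compare groups. The group-by-time interaction compares mean change. The group main effect compares the average of the pre and post values; because randomised groups have the same expected baseline, this halves the treatment difference.

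The interaction is the relevant term, but it subtracts the whole baseline value whatever the correlation between baseline and outcome. When that correlation is modest, the subtraction adds noise. ANCOVA estimates the slope from the data and so does at least as well in large samples. The baseline t tests do not help, since they adjust for nothing.

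At stake is power for the primary comparison in a trial with 34 women per arm expected to complete.

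**Working it through.** **Inputs from the article.** 34 per arm after loss, 1:1 allocation, alpha 0.05 (sidedness not stated; two-sided used here), one pre and one post value.

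**Inputs not in the article, therefore assumed.** Pre-post correlation rho from 0.3 to 0.8, equal SD before and after, and a week-12 difference of d = 0.69 SD. This d is the effect that a plain two-group t test detects with 80% power at 34 per arm. By the normal approximation it is sqrt(2/34) × (1.960 + 0.842) = 0.68.

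**The plan's own figure.** The loss step reproduces: 34/0.8 = 42.5, so 43 per arm and 86 in total. The 34 itself does not follow from the stated 25% to 10%: the standard two-proportion formula gives 100 per group two-sided and 79 one-sided. That is a separate matter. Its relevance here is that section 2.3 supplies no effect on the IEF scale, so d has to be assumed.

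**Variances per woman, in units of the squared SD.**

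- Group-by-time (change score): 2(1 − rho), testing d.
- ANCOVA: 1 − rho², testing d (apart from a small term for estimating the slope).
- Group main effect (mean of pre and post): (1 + rho)/2, testing only d/2.

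The ratio of ANCOVA to change score is (1 − rho)(1 + rho) / [2(1 − rho)] = (1 + rho)/2. This gives 0.65, 0.75, 0.85 and 0.90 at rho 0.3, 0.5, 0.7 and 0.8.

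**Power.** The standardised effect is the difference tested, divided by sqrt(variance × 2/34). At rho 0.5:

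- change score: 0.69 / sqrt(1.00 × 2/34) = 2.84
- ANCOVA: 0.69 / sqrt(0.75 × 2/34) = 3.29
- main effect: 0.345 / sqrt(0.75 × 2/34) = 1.64

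Power from the noncentral t distribution:

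| rho | Group-by-time | ANCOVA | Group main effect |
|---|---|---|---|
| 0.3 | 66% | 84% | 41% |
| 0.5 | 80% | 90% | 37% |
| 0.7 | 95% | 98% | 33% |
| 0.8 | 99.3% | 99.7% | 31% |

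The 80% at rho 0.5 is there by construction, because the change score then has the same variance as the week-12 value alone. In sample-size terms (0.68 SD, normal approximation), 80% power needs 48 per arm for the interaction against 31 for ANCOVA at rho 0.3, 34 against 26 at 0.5, and 21 against 18 at 0.7.

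**If IEF behaves as a skewed count with proportional effects.** Two simulations with overdispersed counts, 34 per arm, all parameters assumed:

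- Baseline mean 10 per week, gamma shape 1.5, response heterogeneity shape 4, rate ratio 0.6, ANCOVA with robust errors, 1,500 replicates. Interaction vs ANCOVA: 32% vs 63% with a 40% fall common to both arms, 48% vs 67% with a 20% fall, 65% vs 70% with none.
- Baseline mean 14 per week, falls of 60% vs 35%, gamma shape 1 or 2, 4,000 replicates. Interaction 21–48%, ANCOVA on raw counts 52–94%, ANCOVA on log(1 + count) 41–86%. Type I error was 4–5% for all.

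ANCOVA leads throughout, but in the first model the gap runs from 5 to 31 points with the common fall alone.

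**The case against.** **The planned test is valid, and the endpoint is defined as change.** Both are true. Type I error of the interaction was 4–5% in the larger simulation and about 6% in the smaller one. But an endpoint worded as change does not require an unadjusted change score: with baseline as covariate, the group coefficient is the same whether the response is week-12 IEF or the change in IEF.

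**A journal article condenses, and a fuller plan may name the tested term or add covariates.** This stands for the unnamed term, which is not pressed here. The baseline t tests also alter no primary result. The choice of model is different: section 2.9 states it, so it can be judged.

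**The size of the gain rests on undocumented inputs.** This stands. The difference of 0.69 SD, rho and every count parameter are assumptions, and at rho of about 0.8 or more with equal variances the gain in power is negligible.

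A reader might infer more than the article supports:

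- *That the analysis is biased or ignores baseline.* It does neither; it subtracts baseline with a coefficient of one.
- *That power is about 37%, or that three P values compete for the primary claim.* The article does not adopt the group main effect as its test, and section 2.9 speaks of differences between groups, which excludes the time effect.
- *That IEF is known to be skewed and the power loss is therefore large.* Skew is plausible for a weekly count, and the success criterion of a more than 50% fall suggests proportional thinking, but no distribution is given.

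**Conclusion.** The point holds as a recommendation on efficiency. The stated model compares groups through an unadjusted change score, although a more precise estimate is available from data that the trial already collects. Under randomisation and equal variances, ANCOVA reduces the variance by 35%, 25% and 15% at rho 0.3, 0.5 and 0.7. For an assumed 0.69 SD difference at 34 per arm, that is 18, 10 and 3 points of power respectively. The direction holds for any rho below 1; the size cannot be fixed from the article. With skewed counts and proportional effects the gap may be larger, but it depends on the assumed parameters. Validity of the planned interaction test is not in question.

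**What to change.** Replace the model sentence in section 2.9 with wording such as:

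> The primary analysis is an ANCOVA of week-12 weekly IEF on treatment group, with baseline weekly IEF as covariate and robust standard errors, reported as the adjusted between-group difference with 95% CI. A count model with log baseline IEF as covariate is supportive.

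If baseline counts of zero can occur, the log term needs a stated offset. The count model is better kept as supportive: a negative binomial Wald test rejected in about 7% of 300 simulated null trials. Robust errors deal with unequal variance and do not turn the additive scale into a proportional one, which is why the count model is worth having.

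Use the same baseline adjustment for the continuous secondary outcomes: perineometry, hiatal area, hiatal diameter and I-QoL. PGI-I has no baseline value and is not affected. If the mixed ANOVA is kept as a secondary analysis, state that group-by-time is its test. The baseline t tests can be dropped in favour of a descriptive table.

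The cost is a change of wording before analysis. No new measurement or visit is needed, and ANCOVA is available in the software named in section 2.9.

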## Discussion

3

The study protocol presents the starting points, design and methods of PFMT with stabilization exercises of high- and low-intensity in women with SUI. We will use the IEF, I-QoL, and PGI-I before treatment and over 12 weeks of treatment.

The strength of the study is objectivization of PF muscle power, endurance and relaxation in units of water column height (cmH_2_O) assessed by perineometry. Examination of HA (in cm^2^) assessed by 3D USG and hiatal diameter assessed by 2D USG.

The methodology section describes the ranking criteria and the methods of enrolment and randomization. Probands will be adult women over 18 years old with uncomplicated SUI. Periodicity of menstruation, surgical gynecological interventions and diseases will be monitored demographically, as well as the number of collection devices. The intervention in both groups will be PFMT with stabilization exercises at two different intensities: Group A, a high-intensity exercise group, 5 times a week for 30 minutes per day and Group B, a low-intensity exercise group, twice a week for 15 minutes per day. The intervention will include the following:

1.Educating women about anatomy, physiology and PF muscle function.2.Training of PF muscles in different positions (lying on back, on abdomen, sitting, standing and walking).3.Training of PF muscles with activation of deep trunk muscles, or stabilization exercises.

Based on similar studies^[2,3]^ we expect good cooperation, low loss and good adherence of probands. The success of treatment will be indicated by a more than 50% decrease of IEF over 1 week.

We expect that, after 12 weeks of high-intensity PFMT, women with SUI will have significantly fewer IEF, better reduction of HA during contraction and VM, higher power and endurance of PF muscles and better QOL compared to the group with low-intensity PFMT.
